### Concealment mechanism {16b}

Allocation concealment will be ensured via a central web-based system (Ennov Clinical® 7.5.720). The treatment to which a patient will be allocated will be disclosed only after enrollment in the study.

### Implementation {16c}

The randomization key will only be known to the biostatistician. Investigators at each study site will be responsible for patient enrollment in the study. Assignment of participants to each study group will be ensured by the central web-based system (Ennov Clinical® 7.5.720®) operated by local investigators, after verification of patient eligibility and inclusion in the study.

## Assignment of interventions: blinding

### Who will be blinded {17a}

Blinding of care providers will be unpracticable as knowledge of the UF_NET_ settings is required to adapt care and apply tested strategies and the hemodynamic protocol. Outcome assessors will not be blinded as group allocation could be deducted from UF_NET_ settings provided in the electronic medical files. Data analysts will be blinded to group allocation, although this may be deducted from the reported fluid balance measurements and applied UF_NET_ rates.

### Procedures for unblinding if needed {17b}

Due to the open design of the study, there is no unblinding procedure. After recording the main outcome criterion of the last included patient into the case report form, a quality control will be performed on the database with blinding of the study arm. Statistical analyses will begin after the database lock.

## Data collection and management

### Plans for assessment and collection of data {18a}

Investigators are responsible for the assessment and collection of outcomes, baseline, and other trial data. To improve the quality of data collected in regard to the hemodynamic protocol and its application every 4 h, a bedside case report form specific to the study arm will be made available, directly downloadable, and printable from the central web-based system Ennov Clinical® 7.5.720 after patient enrollment (Supplemental Materials 4 [intervention group] and 5 [control group], French versions). A laminated print of the hemodynamic protocol of the intervention group will be made available at the bedside of enrolled patients allocated to this group. Data will be entered in the electronic case report form by delegated team members and will be monitored by trained clinical research assistants designated by the sponsor. The digitalized version of the case report form is provided in Supplemental Material 6 (French version). Subjects will be assessed daily while hospitalized in the ICU.

Day 28 and day 90 assessments will be performed by investigators or delegated team members using (in ranked order): electronic medical records, phone calls to the patient’s general practitioner, phone calls to any medical doctor involved in the patient’s care after ICU discharge, and phone calls to the patients or his next-of-kin. A prescription to perform a plasma creatinine concentration measurement at day 90 will be sent by mail to ICU survivors weaned of RRT during their ICU stay, and its results communicated to the general practitioner as well as to the investigators to compute the MAKE-90 secondary outcome. Control of long-term renal function after acute kidney injury is recommended by experts [27].

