#### Efficacy secondary outcomes (study population is given in brackets)

7.Normalized cumulative fluid balance measured in both groups at H24 and H72 after inclusion or death, whichever comes first, and at day 7 in alive patients. Fluid balance measured between inclusion and early time point (H24 or H72 or death) will be normalized by dividing it by the observation period duration and expressed in ml h^−1^. The fluid balance at H24 and H72 will be quantified using the same input and output items as per the primary outcome. The fluid balance at day 7 will be estimated based on the change in body weight between inclusion and day 7 [*ITT population*].8.Normalized cumulative UF_NET_ volume in both study groups at H24 and H72 after inclusion or death, whichever comes first. Cumulative UF_NET_ measured between inclusion and H24 or H72 or death will be normalized by dividing it by the observation period duration and expressed in ml h^−1^. The cumulative UF_NET_ volume will be computed based on the UF_NET_ volumes reported every 4 h between inclusion and 24 or 72 h after inclusion or death, whichever comes first [*ITT population*].9.PaO_2_ to FiO_2_ ratio and the extravascular lung water index measured with the cardiac output monitoring device, measured once a day from inclusion to H72 or death, whichever comes first. The FiO_2_ is the FiO_2_ set on the respirator or the high-flow nasal cannula device. In non-ventilated patients, the FiO_2_ will be estimated using the following formula: FiO_2_ = 0.21 + 0.03 × oxygen flow rate (in L min^−1^) [25] [*ITT population*].10.The number of ventilator-free days in both study groups, quantified as the number of days alive without mechanical ventilation, starting at the time of inclusion and censored at day 28 of inclusion. Mechanical ventilation weaning will be defined if invasive mechanical ventilation is not required for a continuous period of 48 hours or longer. A value of 0 is allocated if the patients died between inclusion and day 28. A value of 0 is also allocated if the patient is still receiving invasive mechanical ventilation at day 28 [24]. In case of multiple mechanical ventilation weaning episodes, only the last weaning attempt will be considered [*ITT population*].11.MAKE-90 assessed between inclusion and day 90 after inclusion in both groups. MAKE-90 comprises death before or at day 90, RRT dependence at day 90, and persistent stage 2 or 3 acute kidney injury (as per the KDIGO guidelines) at day 90. RRT dependence is present if the patient is still receiving CRRT at day 90 or if he has received an intermittent technique in the time frame of ±2 days around day 90. Persistent acute kidney injury is adjudicated based on a baseline plasma creatinine concentration (identified in the 6 months to 7 days before ICU admission), and the plasma creatinine measured at day 90 [6]. In case of missing baseline creatinine value, it will be retrospectively estimated [26]. Each element of the composite event will be evaluated separately [*ITT population*].12.Hospital and ICU length of stay, quantified as the duration, in days, between inclusion and hospital and ICU discharge (alive or deceased), respectively [*ITT population*].

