### Methods in analysis to handle protocol non-adherence and any statistical methods to handle missing data {20c}

The ITT population will consist of all enrolled patients, fulfilling eligibility criteria (inclusion and exclusion), analyzed as per their allocation group, regardless of their adherence to the protocol and the UF_NET_ rates they received, and followed until day 90 after inclusion, loss to follow-up, or death, whichever comes first. All secondary outcomes will be analyzed in the ITT population.

The modified ITT is a subset of the ITT population comprising all patients alive at 72 h of inclusion, fulfilling eligibility criteria (inclusion and exclusion), analyzed as per their allocation group, regardless of their adherence to the protocol and the UF_NET_ rates they received, and followed until day 90 after inclusion, loss to follow-up, or death, whichever comes first. This population hence will not include patients who died before H72 or those who ceased trial participation before H72. The primary outcome will be analyzed in the modified ITT population.

The rate of missing data per variable will be reported. No imputation of missing data is planned, and missing data will not be replaced.

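### The protocol arranges a day-90 creatinine only for patients weaned of RRT in the ICU, so those weaned after ICU discharge have no arranged measurement for the kidney-injury component of MAKE-90

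*Protocol article*

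**What the plan says.** **Endpoint.** Under Efficacy secondary outcomes (#11), the protocol article states: "MAKE-90 comprises death before or at day 90, RRT dependence at day 90, and persistent stage 2 or 3 acute kidney injury". A patient counts as RRT dependent if still on CRRT at day 90, or "if he has received an intermittent technique in the time frame of ±2 days around day 90". Persistent kidney injury is adjudicated from a baseline creatinine "and the plasma creatinine measured at day 90". For the baseline value there is a fallback: "In case of missing baseline creatinine value, it will be retrospectively estimated". None is given for the day-90 value. Each element of the composite is also to be evaluated separately, in the ITT population.

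**Collection.** Under Plans for assessment and collection of data {18a}, a mailed creatinine prescription "will be sent by mail to ICU survivors weaned of RRT during their ICU stay". The result goes to the general practitioner "as well as to the investigators to compute the MAKE-90 secondary outcome". The same section gives a general route for late follow-up: "Day 28 and day 90 assessments will be performed by investigators or delegated team members using (in ranked order): electronic medical records", followed by phone calls to doctors and then to the patient or next-of-kin.

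**Missing data.** Plans to promote participant retention and complete follow-up {18b} lists day-90 creatinine among the values that may be missing, but assigns only vital status and RRT to the ranked retrieval route. Section {20c} adds: "No imputation of missing data is planned, and missing data will not be replaced".

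**The concern.** The group that is sent the test and the group whose endpoint depends on it are not the same. The test goes to patients whose RRT ended in the ICU. The endpoint needs it for all survivors off RRT at day 90, wherever RRT ended.

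The gap is also selective. Whether a patient is sent the test depends on two events after randomisation: when RRT stopped and when the patient left the ICU. The protocol's own efficacy objectives include long-term renal outcome and ICU length of stay, so the strategy is hoped to influence events of this kind. Missingness tied to them could differ between arms, and with about 29 patients per arm a few missing values can alter a comparison of proportions.

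**Working it through.** The documents give no figure for this point, so there is none to reproduce. The check sets the endpoint definition beside the collection rule and follows each type of patient through both.

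**Step 1. Who needs a day-90 creatinine, and who is sent the prescription?**

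| Patient at day 90 | MAKE-90 status settled without creatinine? | Prescription sent under {18a}? |
|---|---|---|
| Died by day 90 | Yes (event) | Not needed |
| Alive, RRT dependent | Yes (event) | Not needed |
| Alive, off RRT, weaned during the ICU stay | No | Yes |
| Alive, off RRT, weaned after ICU discharge and before the day-90 window | No | **No** |

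The RRT-dependence window for an intermittent technique is day 90 ± 2 days, so it opens at day 88. A patient whose last session fell between ICU discharge and day 88 is not RRT dependent and belongs in the last row.

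**Step 2. Can that patient occur under this protocol?** Yes. The section on renal replacement therapy management leaves clinicians free to change to an intermittent technique after 72 h. Section {18b} counts the RRT weaning date among the items that may be missing in survivors after hospital discharge, so weaning outside the ICU appears to be foreseen.

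**Step 3. Does another provision close the gap?**

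- The ranked procedure (records, then calls) can find a result that already exists. It orders no test and does not ensure that a result falls at day 90.
- Section {18b} names vital status and RRT for retrieval by that procedure, not creatinine.
- The estimation rule covers the baseline creatinine only.
- Section {20c} excludes imputation.

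None of these creates the measurement.

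**Step 4. How many patients?** The documents give neither day-90 survival nor the share weaned after ICU discharge. Let *s* be the assumed share of all enrolled patients who are weaned after ICU discharge and alive and off RRT at day 90. With N = 58 (Sample size {14}), the number affected is N × *s*:

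- *s* = 2%: 58 × 0.02 = 1.16, about 1 patient
- *s* = 5%: 58 × 0.05 = 2.9, about 3 patients
- *s* = 10%: 58 × 0.10 = 5.8, about 6 patients

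**Step 5. Share of those who could need the test.** The only mortality assumption in the document is 25% by 72 h, which leaves 58 × 0.75 = 43.5 patients. Day-90 survivors off RRT cannot exceed that number if the assumption holds. The affected share of this group is therefore at least 1.16 / 43.5 = 2.7% at the low end and 5.8 / 43.5 = 13.3% at the high end. It rises with later deaths and with patients still on RRT, for which no rates are given.

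**The case against.** Several points on the other side are fair.

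- **Existing results may be found.** A reader might infer that late-weaned patients can have no day-90 creatinine at all. The text does not support that. The ranked day-90 procedure precedes the prescription rule in {18a} and applies generally, and a routine result may well be on file or known to a treating doctor. What is missing is an arranged measurement. This stands as a limit on the claim.
- **Loss from the composite is an inference.** A reader might also infer that these patients drop out of MAKE-90. The document rules out imputation but does not say how a composite with one unknown element is scored. That rule is commonly left to the analysis plan, which is not shown. Death and RRT dependence remain analysable separately for these patients.
- **Higher risk is plausible, not documented.** It is tempting to state that late recoverers are the patients most likely to have persistent injury. Nothing in the document shows this, nor does it give a direction or size for a difference between arms.
- **The stakes are limited.** One of three elements of a secondary outcome is affected, in a trial sized for 72-hour fluid balance and presented as preparation for a larger one.
- **The article condenses a fuller protocol.** This carries less weight. The sentence in {18a} is a positive and restrictive rule, not an omitted detail, and an analysis plan cannot supply a blood test that was never ordered.

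**Conclusion.** The point holds as a mismatch between a stated collection rule and the endpoint it is meant to serve. Patients weaned between ICU discharge and the day-90 window have no arranged day-90 creatinine. The kidney-injury component, and possibly the composite, may be missing selectively for them, and this could differ by arm.

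The size rests on an assumption: if 2% to 10% of the 58 enrolled patients fall in this group, about 1 to 6 are affected, fewer if routine results are found. The documents support neither a firmer count nor a claim of bias in a known direction. The primary outcome is not touched. The change is worth making because it is cheap and because the value cannot be recovered once day 90 has passed without a test.

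**What to change.** Two edits, both to data collection only:

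1. In {18a}, send the creatinine prescription, ahead of day 90, to every survivor not known to be receiving RRT at that time, wherever and whenever RRT was stopped. The condition has to be RRT status at the time of mailing, because status at day 90 itself is not yet known when the request goes out. A result from a patient who turns out to be RRT dependent at day 90 does no harm, as MAKE-90 is then already met.
2. In {18b}, add day-90 creatinine to the items retrieved by the ranked procedure, next to vital status and RRT.

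The cost is a few more mailed prescriptions and routine creatinine tests. The protocol already notes that experts recommend checking renal function after acute kidney injury. As the trial is enrolling, the change would go through the amendment route in {25}.

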### Plans to promote participant retention and complete follow-up {18b}

Incomplete follow-up during ICU stay is not expected, given the studied population. Given that most outcomes (hemodynamic and physiologic monitoring, CRRT settings including UF_NET_, vasopressor, and mechanical ventilation and their weaning date) are specific to the ICU environment and stay of the participants, we do not expect missing values. Especially, input and output components of the primary outcome measure are reported every 4 h in the electronic ICU medical records and charts, either automatically or by the nursing staff at the bedside.

The procedure regarding the collection of the input and output components of the primary outcome and the procedure in case of missing values are detailed in SM3, Supplemental Table 3.

Missing values at day 28 or day 90 (vital status, day 90 creatinine, RRT weaning date) could occur for surviving patients after hospital discharge. Upon enrollment, patients’ and their next-of-kin contact information will be stored in the digital health record at each study site. Data regarding the vital status and RRT at day 28 or day 90 of inclusion will be retrieved following the ranked procedure described above.

### Data management {19}

An electronic case report form will be created for each included patient using the central web-based system Ennov Clinical® 7.5.720. Subjects will be identified using the first letter of their first name, the first letter of their family name, the center identifier, and the inclusion number. This code will be the only information enabling a retrospective link to the patient. The data collected during the study will be processed electronically in accordance with the requirements of the French Data Protection Authority (CNIL) in compliance with French Reference Methodology MR001. The electronic case report form will be transmitted electronically and centralized in the data management department of the coordinating site. To ensure correct data entry, all data cells of the electronic case report form will be constrained in terms of the number of digits, number of decimal numbers, and range of acceptable values.

### Confidentiality {27}

Subject confidentiality is strictly held by the participating investigators, their staff, the sponsor, and their agents. This confidentiality is extended to cover clinical information relating to subjects, test results of biological samples, and all other information generated during participation in the study. All electronic transmission of data that leaves each study center will be identified only by a unique study identifier that is linked to a subject through a code key maintained at the clinical site, and eventually destroyed at the end of the study. All source records including electronic data will be stored in secured systems.

No identifiable information concerning enrolled subjects will be released to an unauthorized third party. Subject confidentiality will be maintained when the study results are published or presented in conferences. The study monitor, other authorized representatives of the sponsor, and representatives of regulatory agencies may inspect all documents and records required to be conserved by the investigator.

### Plans for collection, laboratory evaluation, and storage of biological specimens for genetic or molecular analysis in this trial/future use {33}

Not applicable. No biological specimen will be collected and stored in this trial. All biological assays reported in the case report forms are those performed in the usual care of critically ill patients with acute circulatory failure and requiring RRT.

## Statistical methods

### Statistical methods for primary and secondary outcomes {20a}

#### General comments and descriptive analysis

All analyses will be performed using the R software for statistical computing (R Core Team). A *p* value < 0.05 will be considered significant.

Patients’ characteristics at enrollment will be reported in each study group to help evaluate allocation balance. Continuous variables will be reported using median and interquartile range (with minimum and maximum values) and compared between the groups using the Mann-Whitney test. Categorical variables will be reported using count and percentage (including missing values) and compared between the groups using the chi-squared test or Fisher exact test, as appropriate. Missing value count and percentage of each reported variable will be given.

#### Primary outcome analysis

The primary outcome measure will be reported with median and interquartile range (with minimum and maximum values) in each study group and compared between groups using Mann-Whitney’s test in the modified ITT population (see section for definition).

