### Sample size {14}

We make the hypothesis that the fluid balance will be of 4000 ± 4000 ml at H72 of inclusion in the control group and that the intervention strategy will generate a fluid balance of 0 ± 4000 ml at H72 of inclusion (absolute between groups difference of 4000 ml). The hypothesis is based on the data reported by a large randomized controlled trial evaluating the timing of RRT in the ICU, in which the H72 cumulative fluid balance was 3711 ml in the early arm and 3917 ml in the delayed arm of the study [18]. Based on this hypothesis, the required sample size to compare two means between two equally sized samples (and a bilateral hypothesis), with a *⍺* of 0.05 and a power 1–*β* of 0.8, would be 16 patients per arm, hence a total of 32 patients. Since (1) we expect a non-survival rate of 25% at 72 h of inclusion (corresponding to the time point of the primary outcome evaluation) and (2) the expected distribution of the primary outcome would not follow the normal distribution, justifying an increase of 25% in sample size, the final total number of patients to enroll would be 58, equally distributed between study groups. Patients deceased before 72 h of inclusion, or alive at H72 but with a missing primary outcome measure, will not be included in the analysis of the primary outcome. Once the required number of 21 patients per arm with an assessable primary outcome will be reached, inclusions will cease.

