## Assignment of interventions: allocation

### Sequence generation {16a}

Allocation sequence will be computer-generated with stratification based on the fluid overload status at the time of enrollment. Fluid overload will be defined as a 10% increase in body weight between ICU admission and trial enrollment [2]. Fluid overload is a known risk factor for ICU mortality. Randomization will be performed in each stratum, with a 1:1 ratio, and using a fixed block size. The block size will only be known by the statistician in charge of the randomization list.

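### The primary Mann-Whitney test ignores the stratified randomisation: it stays valid and well powered, but is conservative and less efficient if fluid overload predicts 72-hour fluid balance

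*Protocol article*

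**What the plan says.** Sequence generation {16a} states: "Allocation sequence will be computer-generated with stratification based on the fluid overload status at the time of enrollment". It continues: "Randomization will be performed in each stratum, with a 1:1 ratio, and using a fixed block size". There are two strata, defined by a 10% weight gain between ICU admission and enrolment. The reason given for the factor is its link with death in the ICU.

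The Primary outcome analysis section fixes both the summary and the test. On the summary: "The primary outcome measure will be reported with median and interquartile range (with minimum and maximum values) in each study group". On the test, the outcome is "compared between groups using Mann-Whitney’s test in the modified ITT population". No stratified or adjusted version is mentioned, and no between-group difference or confidence interval is named. In the analysis plan the stratum returns only under Methods for additional analyses {20b}, as one of eight exploratory subgroups.

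For controls, Sample size {14} assumes 4000 ± 4000 ml. Its assumption for the other arm reads: "the intervention strategy will generate a fluid balance of 0 ± 4000 ml at H72 of inclusion (absolute between groups difference of 4000 ml". Its calculation is two-sided, with alpha "of 0.05 and a power 1–*β* of 0.8, would be 16 patients per arm". Enrolment is 58 patients and stops at 21 assessable per arm.

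**The concern.** Blocking within strata forces the arms to be alike on fluid overload. If that factor also drives the outcome, the rank-sum statistic varies less from trial to trial than the ordinary Mann-Whitney null variance assumes. The test then rejects too rarely under the null and gives up power. With about 42 patients in the primary analysis, information that the design has already secured should not be discarded without a reason.

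There is a second, smaller matter. The trial is sized on a difference in millilitres, and its Discussion says that it should help design a larger trial. Group medians and a rank p value do not give the size of the shift with its precision.

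**Working it through.** **Inputs from the protocol.** Difference 4000 ml, SD 4000 ml, two-sided alpha 0.05, power 0.80, 25% dead by 72 h, a 25% increase for non-normality, 58 enrolled, 21 assessable per arm (Sample size {14}); two strata, 1:1 in blocks (Sequence generation {16a}).

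**Assumptions, not in the protocol.** Overload share in this trial: 25%, borrowed from the prevalence quoted in Background and rationale {6a}, with 50% also tried. Gap in mean fluid balance between strata: 0 to 1.5 SD (0 to 6000 ml). Block size: 4. Outcome: normal, with total within-arm SD held at 4000 ml.

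**The protocol's own figures reproduce.** n per arm = 2 × (1.960 + 0.842)² × (4000/4000)² = 15.7, so 16. With both inflations, 16/0.75/0.75 = 28.4, so 29 per arm and 58 in all. The 21 per arm matches 16/0.75 = 21.3 rounded down.

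**Expected direction.** Let p be the overload share and g the gap in SD units. The stratum explains p(1 − p)g² of the outcome variance. With perfect balance, the null SD of the test statistic shrinks by about √(1 − p(1 − p)g²), so the true level is about 2Φ(−1.96/√(1 − p(1 − p)g²)). For p = 0.25:

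- g = 0.5: √(1 − 0.047) = 0.976, level about 4.5%
- g = 1: √(1 − 0.1875) = 0.901, level about 3.0%
- g = 1.5: √(1 − 0.422) = 0.760, level about 1.0%

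**Simulation.** 8000 trials per cell, 42 assessable patients, large-sample tests without continuity correction. Entries are unstratified Mann-Whitney / van Elteren, in %.

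| Share | Gap (SD) | Type I error | Power at 4000 ml | Power gain from stratifying (points) |
|---|---|---|---|---|
| 25% | 0 | 5.1 / 5.0 | 86.7 / 85.8 | −0.9 |
| 25% | 0.5 | 4.7 / 5.0 | 87.0 / 87.6 | +0.6 |
| 25% | 1 | 2.8 / 4.6 | 88.1 / 91.5 | +3.4 |
| 25% | 1.5 | 1.4 / 4.7 | 91.9 / 97.8 | +5.9 |
| 50% | 0 | 4.9 / 5.0 | 87.2 / 86.2 | −1.0 |
| 50% | 0.5 | 3.9 / 4.6 | 86.7 / 87.5 | +0.8 |
| 50% | 1 | 2.5 / 5.2 | 89.3 / 93.9 | +4.6 |
| 50% | 1.5 | 0.3 / 4.4 | 93.0 / 99.6 | +6.6 |

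The Monte Carlo standard error of one entry is √(0.05 × 0.95/8000) = 0.24 points for the level and √(0.87 × 0.13/8000) = 0.38 points for power. Differences below 1 point should therefore not be over-read.

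**Effect of deaths.** The table does not model deaths before 72 h, which loosen the balance within strata. A separate simulation of 4000 trials per scenario, with 58 randomised and 25% removed as deaths, gave Mann-Whitney levels of 3.4% at a 1 SD gap and 2.0% at 1.5 SD (25% share). The test is then less conservative, in the same direction.

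**The case against.** The strongest objection is that nothing in the plan is invalid. A reader might infer from the mismatch that the error rate, the power or the effect size is mis-stated. The documents support none of the three. The level promised is 5%, and the planned test stays at about 5% or below in every scenario. The power promised is 80%, and the planned test gives about 87 to 93% at 4000 ml. No effect estimate is stated, so none can be wrong; it is unreported. This objection stands in full.

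It is also fair that the loss is conditional. The protocol justifies the stratum by mortality, not by fluid balance. The outcome counts only input and output after inclusion, and a main output, net ultrafiltration, is set by arm. A large stratum gap cannot be presumed: with a 25% share, a gap of 1 SD means that one binary factor explains 19% of the outcome variance, and 1.5 SD means 42%. At 0.5 SD the two tests barely differ. The 25% share is itself borrowed: the background defines overload against premorbid weight, the trial against weight at ICU admission.

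On the missing estimate, this is a condensed article, and a full protocol or SAP may specify a shift with an interval. A difference in medians can also be read off the planned summary, though without an interval.

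The objection does not remove the mismatch itself. The unstratified test is stated outright as the primary analysis, so it is a choice made and not a detail left open. The exploratory subgroup comparison does not repair it, because it does not enter the primary test.

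**Conclusion.** This is a cheap improvement, not a defect of validity. The primary test omits the only factor on which randomisation is stratified. If that factor predicts 72-hour fluid balance, the test is conservative and inefficient: stratifying would gain 3 to 5 points of power at a 1 SD gap and 6 to 7 at 1.5 SD. Up to 0.5 SD, the two tests are within about 1 point of each other either way. The stratified test holds a level of 4.4 to 5.2% throughout.

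These sizes rest on the assumed overload share, stratum gap, block size and normal outcome. The direction does not depend on them, provided that the stratum is prognostic. The absent between-group estimate and interval is a secondary point, since documents not shown may supply it.

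**What to change.** Before database lock, name the rank test stratified by the randomisation factor (van Elteren) as the primary test. Report the stratified Hodges-Lehmann shift in ml with its 95% CI beside the planned medians. As a supportive analysis, fit a linear model of 72-hour fluid balance on arm and stratum, and give the mean difference with its CI, which is on the scale of the sample-size calculation.

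The change is one of wording and needs no new data. It costs about 1 point of power if the stratum is not prognostic. The overloaded stratum may also be small: at a 25% share, 42 × 0.25 = 10.5 patients, or about 5 per arm.
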